#### Cost-effectiveness analysis

A within-trial cost-effectiveness analysis will compare costs and health outcomes of the evidence-based recommendations versus usual care from a health system perspective. The analysis will be conducted from the Australian health system perspective and the time horizon will be 30 days, consistent with the follow-up period of the trial. As such, discounting will not be required. Additional staff time involved with adoption will be estimated using activity logs completed by hospital staff and costed using mid-points of hospital salary ranges. Implementation costs including clinician engagement, and implementation activities will be prospectively recorded. Costs of equipment, materials and consumables, length of stay and readmissions will be retrospectively extracted from department budgets and hospital costing units. Hospital and staffing cost data will remain confidential.

The cost-effectiveness analysis will adopt QALYs as the measure of effectiveness.^39^ QALYs will be estimated using utility scores derived from the EQ-5D-5L questionnaire^39^ within the PRO subgroup across three time points. The EQ-5D-5L is the most widely used health utility tool internationally.^39^ QALYs will be derived by estimating the area under the curve using the methods described by Manca *et al*.^42^ Patients with only a baseline and no follow-up EQ-5D-5L^39^ questionnaires will be excluded from the cost-effectiveness analysis. For patients with one missing follow-up point, utility scores will be imputed using multiple imputation methods.

Results will be reported as incremental cost-effectiveness ratios (ICERs) and net monetary benefits using a willingness to pay threshold of $A50 000 per QALY. To assess uncertainty in the cost-effectiveness outcomes, a non-parametric probabilistic sensitivity analysis will be performed using bootstrapping of individual cost and QALY estimates with 10 000 replications. This will generate 10 000 ICERs which will be plotted on a cost-effectiveness plane and used to estimate mean and 95% CIs for net monetary benefit, along with cost-effectiveness acceptability curves. Where appropriate, one-way sensitivity analyses and scenario analyses will be conducted to assess the impact of key drivers on the cost-effectiveness outcome.

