#### Recruitment

Data collection will occur without direct recruitment of patients, using patient and hospital records with waiver of consent approved by hospital and university ethics committees and with Public Health Act approval. Direct recruitment of patients with informed consent will only be undertaken for the subset of patients invited to participate in data collection required for PROs for inclusion in the economic analysis. Using standard preoperative information methods at each hospital, a study flyer will be provided prior to surgery with contact details of the trial team and a QR code link to the participant information. Informed consent can be provided via hard copy or online consent form, depending on each participant’s preference. The surveys will also be provided via the participant’s preferred mode of contact (via email or text message). Patients who consent to participation in data collection of PROs will be able to withdraw their data at any time up until the point of de-identification, which occurs after the completion of their final survey.

Implied consent will be assumed for clinicians completing the implementation evaluation surveys, including clinicians who are members of Site Implementation Teams. A participant information form for clinicians will be provided with electronic or hard copy survey. Clinicians who participate in implementation evaluation surveys can withdraw their consent until survey submission, at which point data is non-identifiable.

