For the economic evaluation, a randomly selected subsample of up to 1500 patients will be directly recruited to complete PRO surveys, and prospectively followed-up (to allow for incomplete responses). This comprises an average of 300 patients per site over the 27-month trial duration. The sample size for the economic evaluation was determined based on the feasibility of directly recruiting participants with follow-up to 30 days post-surgery.

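### The net-benefit interval rests on a bootstrap of individual patients with no stated site or calendar-time adjustment, and patients with no follow-up EQ-5D-5L are excluded

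*Protocol article*

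**What the plan says.** All of this is in the protocol article.

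- **Contrast.** Under Cost-effectiveness analysis, the within-trial analysis "will compare costs and health outcomes of the evidence-based recommendations versus usual care from a health system perspective". No estimating model is named.
- **Uncertainty.** The probabilistic analysis "will be performed using bootstrapping of individual cost and QALY estimates", with 10 000 replications, and the replicates are "used to estimate mean and 95% CIs for net monetary benefit, along with cost-effectiveness acceptability curves".
- **Missing utilities.** "Patients with only a baseline and no follow-up EQ-5D-5L" "questionnaires will be excluded from the cost-effectiveness analysis". A patient with one missing follow-up point has the utility imputed. Death is not mentioned in this section.
- **Co-primary outcomes.** Under Primary analysis, the models carry a random intercept for site, to handle clustering, and a fixed effect for calendar month, to handle secular trend.
- **Secondary outcomes.** Under Secondary analysis these are to be modelled in a similar way. The outcome types named are binary, count and length of stay; cost and QALY are not named. Survey and activity-log data are to be described by study period.
- **Design.** Under Randomisation, hospitals are the randomised units. There are five.

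**The concern.** In a stepped wedge, control patients come mainly from early months and from late-crossing sites, and intervention patients mainly from late months and early-crossing sites. The protocol recognises this for its co-primary outcomes and gives the reasons for the two model terms. The economic section then goes into detail (resampling unit, number of replications, willingness-to-pay threshold, exclusion rule) and states neither term.

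Followed as written, the natural calculation is to resample patients and take the difference in mean cost and mean QALY between the two periods. Differences between hospitals, and any drift in cost or utility over about 14 months, would then enter the increment. Resampling patients around a pooled difference cannot show the between-hospital part of the variance. The net-benefit interval and the acceptability curve would look more certain than the data allow.

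The exclusion rule raises a separate difficulty. It removes patients because of something that happens after surgery (not answering), and no rule is given for scoring a death.

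**Working it through.** **The plan's own figure.** Sample size determination and power gives up to 1500 survey patients, on average 300 per site. 5 × 300 = 1500, so this reproduces. No standard error, interval or power is given for the economic analysis, so there is no precision figure to reproduce.

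**Inputs from the document.** 27 months; 6-month transition; intervention periods of 6 to 18 months; control starting in month 1 (clusters 1–3), month 4 (cluster 4) and month 7 (cluster 5).

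**Assumptions.** Crossovers are 3 months apart (Figure 1 is not shown). There are exactly 300 patients per site, spread evenly over that site's data months. The outcome is scaled to SD 1. The site ICC for cost or utility is 0.01 to 0.10; the document gives 0.1 for hypothermia and none for cost or QALY.

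**Step 1: who is in each period.** w is each site's share of the period total.

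| Cluster | Control months | Intervention months | Control n | Intervention n | w control | w intervention |
|---|---|---|---|---|---|---|
| 1 | 1–3 | 10–27 | 42.9 | 257.1 | 0.073 | 0.282 |
| 2 | 1–6 | 13–27 | 85.7 | 214.3 | 0.146 | 0.235 |
| 3 | 1–9 | 16–27 | 128.6 | 171.4 | 0.219 | 0.188 |
| 4 | 4–12 | 19–27 | 150.0 | 150.0 | 0.255 | 0.164 |
| 5 | 7–15 | 22–27 | 180.0 | 120.0 | 0.307 | 0.131 |
| Total | | | 587 | 913 | | |

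The weighted mean calendar month is 7.2 for control and 20.9 for intervention, a gap of 13.8 months before rounding.

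**Step 2: standard error of a pooled difference.**

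- Individual bootstrap: √(1/587 + 1/913) = √0.00280 = 0.053 SD.
- True variance with a site effect and no trend: ICC × Σ(w_int − w_ctrl)² + (1 − ICC) × 0.00280, where Σ(w_int − w_ctrl)² = 0.0914.
- Example, ICC 0.05: 0.05 × 0.0914 + 0.95 × 0.00280 = 0.00723, so SE = 0.085.
- Coverage of the nominal 95% interval: 2Φ(1.96 / ratio) − 1.

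| ICC (assumed) | True SE | Ratio to bootstrap SE | Coverage |
|---|---|---|---|
| 0.01 | 0.061 | 1.15 | 91.2% |
| 0.02 | 0.068 | 1.28 | 87.5% |
| 0.05 | 0.085 | 1.61 | 77.7% |
| 0.10 | 0.108 | 2.04 | 66.3% |

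**Step 3: effect of a trend.** Bias = drift per month × 13.8. An assumed drift of 0.005 SD per month gives 0.069 SD, and 0.01 gives 0.138 SD, against a bootstrap SE of 0.053.

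**Step 4: precision once site and time are modelled.** By least squares on the same schedule, the SE is 0.121–0.127 SD with site and linear month, about 2.3–2.4 times the pooled bootstrap SE. With separate month effects it is 0.144–0.151 SD, about 2.7–2.9 times.

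**Step 5: the missing-data rules applied to a death.** A patient who dies before returning any follow-up survey has a baseline only and is excluded. A patient who answers on day 3 and dies before day 30 has one missing point, so a utility is imputed. Neither rule gives the dead patient a utility of 0.

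**The case against.** The strongest reply is that the resampling unit is not in itself the fault. The section does not say how the increment is estimated, and an adjusted model is not ruled out. A simulation on this schedule (300 trials, 200 resamples each) supports the point: an individual bootstrap that refits a site and calendar-month model covers 93–94% at ICCs of 0.01, 0.05 and 0.10. The ratios in Step 2 therefore apply only to an unadjusted pooled difference. That stands, and the finding is conditional on it. It is also fair that the article calls the patient-reported outcomes secondary, so the secondary-analysis paragraph might be meant to reach them, and that a full economic plan may say more. But that paragraph names neither cost nor QALY and sends survey data to descriptive reporting, while the economic section does fix its method in some detail.

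Four stronger readings are tempting, and the document does not support them.

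- *The bootstrap of individuals is invalid in this design.* It is adequate if an adjusted model is refitted in each replicate.
- *The net benefit is confounded.* Bias needs a secular trend, or differences between sites in cost or utility. The document gives no ICC, SD or trend for either.
- *Only surviving responders are valued.* A patient who answers on day 3 and then dies stays in the analysis. Only a death before any follow-up survey meets the exclusion wording.
- *The survey cohort's description is contradicted.* The article says "a randomly selected subsample of up to 1500 patients will be directly recruited to complete PRO surveys", and under Recruitment that "a study flyer will be provided prior to surgery with contact details of the trial team and a QR code link". Random selection of those invited, followed by voluntary consent, fits both.

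**Conclusion.** The point holds in conditional form and is worth correcting before the economic analysis is run. The economic section states an individual-level bootstrap and no site or calendar-time adjustment, in a trial of five randomised hospitals whose co-primary models require both. If the increment is the pooled difference, the periods compared are about 14 months apart with a different hospital mix, and the nominal 95% interval covers about 91% down to 66% for site ICCs of 0.01 to 0.10, even with no trend. These sizes rest on the assumed 3-month steps, equal and even recruitment, and the assumed ICC range. The direction does not depend on the exact ICC: the interval was too narrow at every value tried.

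The exclusion of patients with no follow-up questionnaire is stated outright and is a complete-case restriction. Its effect on the QALY difference cannot be sized, because the document gives no non-response or mortality figure. The treatment of deaths is inferred from the wording of two rules that would handle early and later deaths differently. The co-primary results are not affected.

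**What to change.** 1. Estimate incremental cost and incremental QALY by regression with site and calendar-time terms, and baseline utility as a covariate. Express costs in one price year.
2. Keep the bootstrap, but refit that model in every replicate and resample within site-by-period cells. Alternatively, use another method that respects the five sites, with a small-cluster correction. Resampling five whole sites is itself unreliable.
3. Set utility to 0 from the date of death and keep those patients, whenever in the 30 days the death occurs.
4. Multiply impute the other patients with a baseline but no follow-up survey, instead of excluding them.

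The cost is more analysis work and a wider interval: under the assumptions above, a standard error about 2.4 times the pooled bootstrap one with linear month, and up to about 2.9 times with separate month effects. No change to design or recruitment is required.

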### Patient and public involvement

Patients and the public were not involved in the development of this study protocol. However, patients were involved in the development of the simple principles and recommendations,^18^ which will be evaluated in this trial. Plain language summaries of study findings will be developed for participants and wider patient communities to supplement planned publications.

## Ethics and dissemination

The study has obtained full ethical approval with waiver of consent from Metro North B Human Research Ethics Committee (reference: HREC/2023/MNHB/94571) and institutional administrative ethical approval. A waiver of consent was approved on the basis that the research carries no more than low risk to participants,^43^ the benefits from the research outweigh the risks of not seeking consent, it is impractical to seek consent due to the number of participants and records and there is sufficient protection of privacy and confidentiality.^43^ Site-specific, governance approvals have been obtained at each participating hospital. Queensland’s Public Health Act 2005 approval has also been granted for access to patient data. Any risk associated with access to data is minimised through the de-identification of data and ensuring data is accessed and stored according to the Australian Code for the Responsible Conduct of Research.^44^

Our dissemination plan includes strategies to support translation of findings into practice (where appropriate), as well as local, national and international dissemination across all relevant professional groups. If trial outcomes demonstrate benefit, we will disseminate the recommendations and implementation strategy to health services across Australia, drawing on the professional networks held by our large, interdisciplinary partnership team. The intent of this approach is to facilitate translation of results via diffusion, dissemination, implementation, thus promoting sustainability. For local dissemination at each hospital trial site, we will produce reports, presentations and plain language summaries. Our national and international dissemination includes submitting our findings for publication and presenting our work at relevant national and international health services conferences. Relevant reporting guidelines will be used in publications, as appropriate, including the Sex and Gender Equity in Research guidelines.^45^

## Discussion

Perioperative hypothermia prevention is complex. Our implementation design promotes coordinated action for hypothermia prevention across the surgical journey. Frontline teams will adapt implementation of guidance to suit their context. An external–internal facilitation model will support interdisciplinary team-based implementation at each site, guided by the KTA framework.^23^

Our effectiveness-implementation study will evaluate outcomes with a stepped-wedge cluster trial design. This allows all hospital sites to begin implementation at different times, with each site acting as its own control. By using hospital data collected for routine care, we maximise trial feasibility, but outcome evaluation relies on completeness of patient and hospital data sets. Some other potentially valuable outcomes of hypothermia prevention fall outside the scope of this trial, for example, patient-reported thermal comfort or shivering. These outcomes require prospective data collection methods that are not feasible within our trial design.

The GLOW trial is built on strong collaborative research partnerships between health services, universities and government organisations seeking to eliminate preventable perioperative hypothermia. It will contribute to our nascent understanding of how to bring about sustainable practice change for perioperative patient safety.
